### Statistical analysis

In objective 1 we will use a Cox proportional hazard model with age as the underlying timescale to investigate the hazard of childhood haematopoietic neoplasms in children born before and after the iTFA ban, as a proxy for iTFA exposed or not exposed in fetal life. Observations will be censored in case of death, immigration or at 7 years of age. To take the potential secular trend in the incidence of haematopoietic neoplasms into account we will model the variation in cancer risk across birth cohorts by a piecewise linear spline with a knot at 1st of September 2004. Further, we will investigate incidence trends over time.

By examining *all* children from the entire national birth cohorts it is reasonable to assume that all confounding variables will be equally distributed among the exposed and non-exposed individuals, but still we will investigate potential influence of secular variation or possible confounding effects which might have changed during the time period and which might be associated with both TFA exposure and haematopoietic neoplasms. Such potential confounders could be age of the mother at the time of giving birth, assuming accumulation of TFA with age and an older age for first time pregnancies over time. The median gestational age might have increased during the investigated time period, which would increase the average intrauterine exposure to TFA over the study period [44]. Smoking status during pregnancy might have decreased over time and smoking might be associated with increased cancer risk, smoking is also associated with gestational age and thereby with the length of the TFA exposure during pregnancy.

As sub-analysis we will exclude cancer cases diagnosed before the 90 day of life since the origin most likely is due to chromosomal alterations leading to oncogene activation [37]. If feasible we will investigate the first born only since some studies have shown higher risk of childhood cancers in the first born compared to their younger siblings [45] and sensitivity analysis of sub-types of haematopoietic neoplasms (leukemia and lymphoma). Further, we will investigate children with early diagnosis, e.g. before age 4 years.

Conditional logistic regression analyses will be used in the 2nd objective to compare blood spot fatty acid levels between subjects with haematopoietic neoplasms and matched subjects who have not developed cancer. We will investigate industrial as well as ruminant TFA independently and mutually adjusted. Based on a priori consideration we will adjust for maternal and paternal age, smoking during pregnancy, birth weight and gestational age. Also, there might be regional and urban/rural differences in iTFA intake. Place of residence is available from Statistics Denmark, and can be included into analyses. Diets are usually different between families with higher and lower socioeconomic status and maternal socioeconomic status may influence intake of certain food products rich in trans-fat. Information on socioeconomic status, education and ethnicity is available from Statistics Denmark and can be controlled for.

As mentioned in the methods description, other fatty acids potentially related to haematopoietic neoplasms in children will be analysed in the DBS since our methodology allows a complete separation, identification and quantification of sixty fatty acids. We will therefore also investigate interactions between TFA and polyunsaturated fatty acids, and risk of haematopoietic neoplasms in children as well as association between polyunsaturated fatty acids and risk of cancer stratified by trans fatty acids.

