Studies demonstrating relationships between trans-fat intake and cancer in childhood are lacking. However, evidence has shown some possible negative effects on other health outcomes among children. Bouwstra and colleagues have shown that neonates with high TFA umbilical levels have a less favorable neurologic condition at 18 months [27]. Furthermore, a recent review (including human and animal studies) concluded that fetal exposure to trans-fat appears to increase the offspring risk for developing metabolic diseases throughout life [28]. TFAs also interfere in the metabolism of long-chain polyunsaturated fatty acids which might result in a negative impact on infant growth and development [29, 30]. Lifelong, including prenatal, consumption of a diet rich in polyunsaturated fatty acids (PUFA, contained in nuts, seeds and fish) has been shown to protect against tumor growth and to modify glucose metabolism in Walker tumor cells and lymphocytes in Wistar rats [31]. Therefore, the inhibitory effect of PUFA and their interference with trans fatty acids might also be relevant in the fetal programming of childhood cancers.

Despite a general reduction in the iTFA use in food production, Denmark, as the first EU country, legislated against the use of iTFA in all Danish and imported human foodstuffs [32]. The order came into effect on March 31st, 2003, with a transition period until January 1st, 2004. The order imposed a maximum of 2 g of iTFA/100 g oils and fats. During the transition period a maximum level of 5% iTFA was allowed in foodstuffs also containing ingredients other than oils and fats [32]. This legislation led to a radical reduction of iTFA from margarine and shortenings which resulted in a rapid decline in products with trans-fat followed by a decrease in population-level CVD mortality rates [33].

Despite the alarming evidence of increased risk of several diseases caused by TFA consumption and the fact that millions of people still have a too high iTFA intake in Europe, currently no EU legislation regulates the content of iTFA in food products [34].

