**Fig. 1 Fig1:**

Constitution of the exposed versus non-exposed groups of cases who developed haematological malignancy before the age of 7 years and registered in The Danish Cancer Registry (Objective 1)

The incidence of childhood haematopoietic neoplasms among 1,101,055 individuals from the period before the iTFA legislation born between January 1st, 1988 and August 31st, 2004, will be compared to the incidence of childhood haematopoietic neoplasms among 276,422 individuals from the period after the iTFA legislations born between September 1st, 2004 and December 31st, 2008, as a proxy of iTFA gestationally exposed or not exposed, respecitvely. In this overall time period approximately 740 incident haematopoietic neoplasms cases occurred in children before the age of 7 years.

*The second objective* is a case-control study investigating biomarkers of neonatal trans-fatty acid concentrations from stored DBS [34] from individuals who developed childhood haematopoietic neoplasms before the age of 7 years and born in the period 1988–2008 compared to matched controls (Fig. 2).

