## Discussion

Our main goal for this study is to strengthen the scientific basis for understanding idiopathic haematopoietic neoplasms in children. By presenting the protocol before undertaking the actual analyses, we intend to improve the quality, integrity and transparency of the study.

Strengths of the first objective include the unselected national cohort, the prospective design and the register-based measure of outcome. This explorative study takes advantage of the iTFA elimination policy implemented in Denmark almost fifteen years ago, and nests this “societal experiment” in a setting where the effect of conditions from conception (and before) for development of certain diseases can be followed among individuals from birth and onwards. The study is possible due to complete identification of every resident in Denmark via a civil registration number. This number can be linked, on an individual level, to Danish birth, patient and medical registries; social and ethnic registries; and clinical and other national databases. The comprehensive linkage of datasets for both aims makes it possible to study mediation, confounding and/or modification of effects of iTFA for childhood haematopoietic neoplasms.

For the first objective we do not collect any individual data on iTFA intake. In contrast, all individuals are unselected in relation to iTFA exposure and later disease occurrence. This may be considered a very strong feature of the present study, as neither confounding from external or internal factors, nor the lack of individual data on iTFA intake, is a prerequisite for the study, as the influences of lifestyle differences (e.g. use of infant formula, individual diet intake, use of supplements), or biological (adipose tissue stores, weight changes during pregnancy and post-partum) which we would not be able to adjust for, are all independent of the iTFA legislation.

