Nevertheless, the proposed study design, especially in the first objective, also implies some uncertainties, including a potential ecological fallacy. The exposure measure is applied equally to all members of the cohort before and after the ban, while the individual exposures have probably differed. However, a previous study has shown a marked decline of average iTFA intake resulting in elimination after the ban [32]. In the case-control study we investigate TFA exposure individually in all cases from 1988 to 2008. The variations in the exposure observed in the case-control study will then inform our assumptions taken in the cohort study.

Any societal changes preceding 1988 or succeeding 2008 will influence the exposed and control groups similarly, while results will be confounded by any potential societal changes occurring around the time where the trans-fat ban was implemented (e.g. 2003/04). However, we are unaware of such changes except for a screening for DS which we have taken into account by excluding children with DS.

Potentially exposure to TFA from maternal adipose stores could affect the “unexposed” group (born after the ban of iTFA) and postnatal influences like maternal feeding practice and weight gain, may also influence cancer risk through a non-TFA mechanism. Although this may indeed seem a possible limitation, since literature has shown that weight loss of the mother (e.g. during lactation) liberates TFA fat deposits [44], proper randomization in our societal experiment study is mimicked by separating exposed and non-exposed individuals by one point in time with a minimum of selection bias. Thus, it is an obvious strength to the present research design, that the individuals will be unselected, and generally representative of the Danish population, in relation to exposed vs. non-exposed to the trans-fat legislation, as well as to the development of haematopoietic neoplasms. However, since we do not know the exact mechanism between TFA and childhood neoplasms, we cannot account for a residual confounding which might affect observed associations. Residual confounding could be caused by additional components in food products with high contents of TFA. We are not able to investigate TFA levels at specific developmental stages during gestation, but since no knowledge exist on specific target windows for childhood cancers, this may not be relevant.

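### Objective 1 reads a before/after-ban birth contrast as fetal exposure, but the ban also changed the children's own iTFA intake, so its hazard ratio is a combined prenatal and postnatal effect

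*Protocol article*

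**What the plan says.** In the Statistical analysis section, objective 1 is a Cox model on age that compares children born before and after the ban "as a proxy for iTFA exposed or not exposed in fetal life". The groups are "1,101,055 individuals from the period before the iTFA legislation born between January 1st, 1988 and August 31st, 2004" and "276,422 individuals from the period after the iTFA legislations born between September 1st, 2004 and December 31st, 2008" (Study population, text at Fig. 1). Birth-cohort variation is to be modelled by a piecewise linear spline with a knot at 1 September 2004. No term for postnatal exposure is described. The opening of the Methods reads objective 1 as an effect on fetal programming.

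The Background says that Denmark "legislated against the use of iTFA in all Danish and imported human foodstuffs", and "The order came into effect on March 31st, 2003, with a transition period until January 1st, 2004". Study population sets censoring at age 7.

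The Discussion lists infant formula, individual diet and supplements among influences that "are all independent of the iTFA legislation". It names uncertainties "including a potential ecological fallacy", raises TFA released from maternal fat stores, and says that postnatal factors such as feeding practice and weight gain "may also influence cancer risk through a non-TFA mechanism". It does not mention the child's own iTFA intake.

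**The concern.** A law that removed iTFA from food changed what children ate as well as what pregnant women ate. Most children in the exposed group met iTFA in the womb and then at the table for part or all of follow-up. Children in the unexposed group lived entirely after the ban. One birth-date term cannot tell these two windows apart, so a purely postnatal effect would show up in the term that the protocol labels fetal.

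The study's hypothesis concerns fetal development, and the abstract looks ahead to preventive action on the mother's diet. A positive objective 1 result would support a benefit of the ban. It would not by itself show that pregnancy was the relevant window.

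**Working it through.** **The plan's own figure.** Power calculation gives a least detectable HR of 1.35 (80% power, 5%). With about 740 events and group shares 0.7993 and 0.2007, Schoenfeld's formula gives exp[√(7.849 / (740 × 0.7993 × 0.2007))] = exp(0.257) = 1.29. Freedman's gives 1.32. The stated 1.35 is not reproduced exactly but is conservative. It serves here only as a yardstick.

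**Inputs from the protocol.** Cohorts of 1,101,055 and 276,422, about 740 events, follow-up to age 7, end of the transition period 1 January 2004.

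**Assumptions of this check.** Births even within each period, flat incidence by age, no death or emigration, no prenatal effect, and a postnatal rate ratio (RR) of 1.35. The RR is illustrative; the protocol gives none.

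**Step 1: pre-ban share of person-time.** The exposed group spans 200 birth months.
- Births 1988–1996 (108 months): follow-up wholly before 2004.
- Births 1997–2003 (84 months): on average half before.
- Births January–August 2004 (8 months): none before.

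Share before the ban = (108 + 42) / 200 = 75%. In the unexposed group it is 0%. With 31 March 2003 as the date, the exposed share is 70.5%.

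**Step 2: false HR in the plain contrast.**
- Current exposure acts: 1 + 0.75 × 0.35 = 1.26. For RR 1.2 and 1.5 it is 1.15 and 1.375. With the 2003 date and RR 1.35 it is 1 + 0.705 × 0.35 = 1.25.
- Any past exposure acts: 192 of 200 birth months precede the ban, so 1 + 0.96 × 0.35 = 1.34.

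**Step 3: does splitting follow-up at 1 January 2004 cure this?** In the split model without a birth trend, the prenatal term compares the exposed group's post-ban person-time with the unexposed group. That post-ban time amounts to 42 + 8 = 50 birth-month units, of which 42 / 50 = 84% belongs to children already born before the ban.
- Current exposure: 1.00.
- Any past exposure: 1 + 0.84 × 0.35 = 1.29.

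An expected-count Poisson model on birth-month by age-month cells gives the remaining entries. Fraction of life enters as 1.35 raised to that fraction.

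| Postnatal mechanism, RR 1.35 | Plain | Step + linear birth trend | Split | Split + trend |
|---|---|---|---|---|
| Current exposure | 1.26 | 1.05 | 1.00 | 1.00 |
| Fraction of life exposed | 1.30 | 1.15 | 1.14 | 1.13 |
| Any past exposure | 1.34 | 1.29 | 1.29 | 1.28 |

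If a step is added to the planned spline with its knot at 1 September 2004, the false step is 1.09 (current) or 1.30 (any past).

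**Step 4: cost in precision.** Person-years are 5,780,539 (exposed, pre-ban), 1,926,846 (exposed, post-ban) and 1,934,954 (unexposed). With RR 1.35 acting on the first cell, the 740 events divide into about 495.0, 122.2 and 122.7. Detectable HR = exp(2.80 × SE).
- Unsplit: SE = √(1/617.2 + 1/122.7) = 0.099, HR 1.32.
- Split: SE = √(1/122.2 + 1/122.7) = 0.128, HR 1.43.
- With a linear birth trend, from the model: 1.46 unsplit, 1.47 split.

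The unsplit 1.32 exceeds the 1.29 above because this scenario leaves fewer events in the unexposed group.

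**Step 5: the births between the two dates.** Children born January–August 2004 are the only ones classed as exposed before birth but not after. They are 8 / 200 = 4% of the exposed group. If there is no effect, they have about 0.04 × 591.5 = 24 events against 148.5 in the unexposed group, for a detectable HR of about 1.86. That is too few to settle the question.

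**The case against.** **Trend adjustment already helps.** The plain contrast is not the whole plan. If only current exposure acts, a birth trend cuts the false HR from 1.26 to 1.05, because such an effect fades in gradually over births 1997–2003. This stands, but only for that mechanism. For any past exposure 1.29 remains.

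**The protocol does not lean on objective 1 alone.** Its Hypotheses section frames objective 1 as a population-level effect of reduced iTFA use. The Methods say the two objectives reinforce each other, and the Discussion says the case-control results will inform the cohort assumptions. Objective 2 measures newborn blood in pairs matched on birth date, so ban timing is balanced within pairs. This stands. A reader might infer that the prenatal question, or the message on maternal diet, collapses without a postnatal term. The protocol does not support that, since objective 2 addresses the prenatal window directly.

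**The limitation is already conceded.** It is not. The ecological fallacy in the Discussion concerns differences between individuals at a given time, and the postnatal influences it names act by a route other than TFA. The independence sentence can be read as being about lifestyle differences between families. Even so, it cannot hold for the child's iTFA intake, given the Background's account of the law and the Discussion's own reference to a marked fall in average intake.

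**The early-diagnosis analysis (before age 4) and the exclusion of cases before day 90** are not offered as ways to separate the two windows.

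**Conclusion.** The point holds as a matter of interpretation and of one incorrect statement. The objective 1 HR estimates the combined prenatal and postnatal effect of the ban. Under the stated assumptions, a postnatal RR of 1.35 alone yields a false prenatal HR of 1.26 to 1.34 in the plain contrast and 1.05 to 1.29 with a step plus linear birth trend. The upper ends come close to the protocol's own detectable HR of 1.35. Whether any postnatal effect exists is unknown.

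A reader might infer that splitting follow-up at the ban separates the two windows, so that an effect surviving the split can be called prenatal. The design does not support this. Only births 1997–2003 straddle 1 January 2004, 84% of the prenatally exposed post-ban person-time belongs to children already born before the ban, and no child has postnatal exposure only. If exposure accumulates or its effect persists, the split still leaves 1.14 or 1.29. Once a birth trend is in the model, the split changes little outside the current-exposure case. Persistence is necessary but not sufficient for a prenatal reading.

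**What to change.** 1. Correct the Discussion: take the child's own iTFA intake out of the influences said to be independent of the legislation, and name postnatal iTFA intake as a limitation of objective 1.
2. Describe the objective 1 HR as the combined prenatal and postnatal effect of the ban, and rest prenatal attribution on objective 2.
3. Prespecify a sensitivity analysis with follow-up split at 1 January 2004 and a time-dependent postnatal term, plus a cumulative or lagged version. Report the birth-date HR with and without these terms, and state that persistence alone does not establish a prenatal effect.

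The first two items cost only wording. The third needs one person-time split in register data already to be linked. Its price is precision for the prenatal term: the detectable HR rises from about 1.32 to 1.43 without a birth trend, or from 1.46 to 1.47 with one. As a sensitivity analysis, it leaves the primary comparison's power untouched.

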### Study population

The cancer registry is complete until December 31st 2015. To secure equal time of follow-up for cancer diagnosis in all individuals we censor at 7 years of age, which is the longest follow-up time in which we have information on possible cancer outcomes for all individuals.

We will exclude all children born with a Down’s Syndrome (DS) diagnoses due to their increased risk of childhood leukemia [35] and due to secular trends in DS incidence, because of a new screening practice for DS and other chromosomal aberrations introduced in 2004.

*In the first objective,* national birth cohorts of individuals born between January 1st, 1988 and December 31st, 2008 in Denmark will be included (Fig. 1). This is a register based study using the Danish civil registration number which will be linked to the Danish National Cancer Register, where the cancer patients are followed-up until December 31st, 2015.

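### The objective 1 censoring rule lists immigration where emigration is needed, so children who leave Denmark would, read literally, stay at risk as cancer-free person-time

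*Protocol article*

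**What the plan says.** The Statistical analysis section states that for objective 1 "we will use a Cox proportional hazard model with age as the underlying timescale", and gives one rule for leaving the risk set: "Observations will be censored in case of death, immigration or at 7 years of age".

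The Study population section defines who enters: "individuals born between January 1st, 1988 and December 31st, 2008 in Denmark will be included". Cancer outcomes come from linkage to the Danish National Cancer Register through the civil registration number. The Discussion attributes the completeness of this linkage to the identification of residents of Denmark.

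The Study population section also explains the age limit: "To secure equal time of follow-up for cancer diagnosis in all individuals we censor at 7 years of age". It supports the choice of seven years by noting that no longer period is covered by outcome data in every child. On the data cut it says: "The cancer registry is complete until December 31st 2015".

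**The concern.** Every cohort member is born in Denmark and is at risk from birth. For such a child, immigration can only mean coming back after a stay abroad. That is when register observation resumes, not when it ends. Observation ends at emigration, which the rule omits and which appears nowhere else in the article.

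Run literally, the rule fails in two ways. A child who leaves keeps contributing cancer-free time up to age 7, although a diagnosis abroad would not be expected to reach the register. A child who returns could be censored on arrival, just when a diagnosis could again be recorded.

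What is at stake is the before/after hazard ratio. If more post-ban than pre-ban children leave before age 7, the post-ban rate is understated by more. That pushes the result towards the study hypothesis of lower risk after the ban.

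**Working it through.** **Reading the sections together.** Entry is by birth in Denmark (Study population), ascertainment is by a national register (Study population), and exit is at death, immigration or age 7 (Statistical analysis). With entry at birth, emigration is the only migration event that ends ascertainment, and it is the one missing. That diagnoses abroad are not captured is inferred from the register being national and from the Discussion's reference to residents. The article does not say so directly.

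**Size of the emigration effect.**

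The article gives no emigration figures, so these inputs are assumptions: 2-3% of pre-ban and 3-6% of post-ban children leave before age 7, at times uniform over the seven years, with no return.

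- If a share *e* leaves at uniform times, the fraction of counted person-time spent abroad is q = e/2. Pre-ban q = 0.010 to 0.015; post-ban q = 0.015 to 0.030.
- With a roughly constant rate, each period's estimated rate is multiplied by (1 - q), and the post-ban versus pre-ban hazard ratio by (1 - q_post)/(1 - q_pre).

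| Pre-ban leave | Post-ban leave | Factor on hazard ratio |
|---|---|---|
| 3% | 3% | 0.985/0.985 = 1.000 |
| 2% | 3% | 0.985/0.990 = 0.995 |
| 3% | 6% | 0.970/0.985 = 0.985 |
| 2% | 6% | 0.970/0.990 = 0.980 |

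The bias is therefore 0 to about 2%. Expressed as exposed versus unexposed, the extreme is 0.990/0.970 = 1.021.

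A wider assumption, set directly on the share of person-time abroad, gives 0.98/0.99 = 0.990 for 1% versus 2%, 0.95/0.98 = 0.969 for 2% versus 5%, and 0.95/0.99 = 0.960 for 1% versus 5%. Equal shares in the two periods leave the hazard ratio unchanged at any level of emigration.

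**The age-7 limit.** The last birth is on 31 December 2008 and the register is complete to 31 December 2015, a difference of 7.0 years. The article's figure reproduces. The same limit applies to the approximately 740 cases (text with Fig. 1) and to the objective 2 case definition.

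**What longer follow-up would add.**

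- The first post-ban birth, 1 September 2004, reaches 11.33 years at the data cut.
- The group sizes are 1,101,055 and 276,422 (text with Fig. 1), so the post-ban share is 276,422/1,377,477 = 0.2007.
- Extra post-ban person-years with uniform births: 276,422 × (11.33 - 7)/2 = 598,454, which is 31% of 276,422 × 7 = 1,934,954.
- Extra pre-ban person-years to the same age: 1,101,055 × 4.33 = 4,767,568.
- Average rate under 7: 740/(1,377,477 × 7) = 76.7 per million person-years.
- If the rate at ages 7-11 is 35-70% of that (assumed), there are about 16-32 further post-ban and 128-256 further pre-ban cases.
- Baseline information is 740 × 0.2007 × 0.7993 = 118.7. Integrating rate × number at risk × p(1 - p) over ages 7 to 11.33, where p is the post-ban share still at risk, adds 12-23%.
- By Schoenfeld's formula (two-sided 5%, 80% power, no trend adjustment), the least detectable hazard ratio moves from 1.29 to between 1.28 and 1.26.

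**The case against.** The strongest reply is that this is a one-word slip that a competent analyst would correct without being told, and that its effect is small beside the least detectable hazard ratio of 1.35 in the Power calculation section. The size argument stands: a bias of at most about 2% under the main assumptions would not change the conclusion. A further mitigating point also stands in part. The model includes a piecewise linear spline across birth cohorts with a knot at 1 September 2004, and a gradual change in emigration would be partly absorbed by it. The figures above are for an unadjusted contrast.

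The reply does not remove the point. The sentence is the only definition of exit for the objective 1 model. The article presents itself as a statement of the analysis before it is run and undertakes to update the protocol if the analysis deviates. An analyst who sensibly censors at emigration would be departing from the published text.

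Two stronger readings are tempting and not supported. A reader might infer that the rates will be understated by an amount that differs between periods. That needs the sentence to be coded literally, and it needs emigration to differ between the birth periods; the article shows neither. A reader might also infer that stopping at age 7 is a mistake because a Cox model on the age scale does not need equal follow-up. It does not need it, but that makes the limit optional rather than wrong. The limit is stated with a reason, agrees with the dates, gives both objectives one outcome definition, and suits a hypothesis about prenatal exposure.

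**Conclusion.** The censoring rule is wrong as written: it names an event that is not a loss to follow-up for children born in Denmark and leaves out the one that is. It is a small correction to an operative sentence, and it should be made. If the rule is coded literally, each period's rate is understated. The hazard ratio is affected only through a difference in emigration between the periods: about 0-2% under the assumed 2-3% versus 3-6%, up to 4% under the widest assumption tried, and zero if emigration is equal. These sizes rest on assumed emigration and on an unadjusted comparison. The age-7 limit is not a finding. Longer follow-up would bring a modest gain in precision that itself depends on an assumed rate after age 7.

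**What to change.** In the Statistical analysis section, replace immigration with emigration, so that a child is censored at death, the date of first emigration or the seventh birthday, whichever comes first. Adding 31 December 2015 to this rule would change nothing, because the youngest child turns 7 on that day. The cost is one word. The present rule already presupposes that migration dates are available. A case diagnosed after a child has left and returned would no longer count; the article gives no basis for estimating how many there are.

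Optionally, add a secondary sensitivity analysis for objective 1 that follows all children to 31 December 2015 on the age scale, with under 7 kept as the main result. It needs register follow-up beyond age 7. Later diagnoses may be less closely tied to prenatal exposure, and beyond about 11.3 years no post-ban child remains at risk, so later pre-ban cases add nothing to the direct comparison. The wording correction should be made whether or not this analysis is taken up.
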